## Abstract

**Background:**

Deep muscle relaxation has been shown to facilitate operating conditions during laparoscopic surgery. Minimally invasive esophageal surgery is a high-risk procedure in which the use of deep neuromuscular block (NMB) may improve conditions in the thoracic phase as well. Neuromuscular antagonists can be given on demand or by continuous infusion (deep NMB). However, the positioning of the patient often hampers train-of-four (TOF) monitoring. A continuous infusion thus may result in a deep NMB at the end of surgery. The use of neostigmine not only is insufficient for reversing deep NMB but also may be contraindicated for this procedure because of its cholinergic effects. Sugammadex is an effective alternative but is rather expensive. This study aims to evaluate the use of deep versus on-demand NMB on operating, anaesthesiologic conditions, and costs in patients undergoing a two- or three-phase thoracolaparoscopic esophageal resection.

**Methods/Design:**

We will conduct a single-center randomized controlled double-blinded intervention study. Sixty-six patients undergoing a thoracolaparoscopic esophageal resection will be included. Patients will receive either continuous infusion of rocuronium 0.6 mg/kg per hour (group 1) or continuous infusion of NaCl 0.9 % 0.06 ml/kg per hour (group 2). In both groups, on-demand boluses of rocuronium can be given (open-label design).

The primary aim of this study is to compare the surgical rating scale (SRS) during the abdominal phase. Main secondary aims are to evaluate SRS during the thoracic phase, to evaluate anesthesiologic conditions, and to compare costs (in euros) associated with use of rocuronium, sugammadex, and duration of surgery.

**Discussion:**

This study is the first to evaluate the benefits of deep neuromuscular relaxation on surgical and anaesthesiologic conditions during thoracolaparoscopic esophageal surgery. This surgical procedure is unique because it consists of both an abdominal phase and a thoracic phase taking place in different order depending on the subtype of surgery (a two- or three-stage transthoracic esophagectomy). In addition, possible benefits associated with deep NMB, such as decrease in operating time, will be weighed against costs.

**Trial registration:**

European Clinical Trials Database (EudraCT) number: 2014-002147-18 (obtained 19 May 2014)

ClinicalTrials.gov: NCT02320734 (obtained 18 Dec. 2014)

## Background

Deep muscle relaxation has been shown to facilitate surgical field visibility and operating conditions as measured by the surgical rating scale (SRS) during laparoscopic surgery [1–5]. However, most of these studies were short-lasting low-risk procedures such as laparoscopic cholecystectomy. Minimally invasive thoracolaparoscopic esophageal surgery is a high-risk procedure in which the use of deep neuromuscular block (NMB) may also increase field visibility and improve anaesthesia conditions such as straining, high peak insufflation pressures, and respiratory and cardiac incidents [1–5]. However, the positioning of the patient (prone and supine with both arms alongside the body) during this procedure often hampers accurate train-of-four (TOF) measurement to evaluate the depth of the NMB. During these surgical procedures, boluses of muscle relaxants are often given randomly or on indication only, at the discretion of the surgeon or anaesthesiologist. Alternatively, continuous infusion of rocuronium can be used but this might result in a deep NMB at the end of surgery, leading to a prolonged emergence from anaesthesia. To reduce post-operative respiratory complications, but also to facilitate rapid extubation of the trachea rather than post-operative mechanical ventilation in the intensive care unit (ICU), neuromuscular antagonists are often needed.

The use of neostigmine not only is insufficient for reversing deep NMB but also is contraindicated for moderate NMB because of its cholinergic effects on smooth muscle that may increase the risk of anastomotic dehiscence, although the evidence is conflicting [6–8]. In addition, neostigmine may be associated with increased risk of respiratory complications post-operatively because of high incidence of residual neuromuscular relaxation [9]. Sugammadex is a safe and effective alternative to neostigmine but is rather expensive. Based on the high costs of sugammadex, the administration of rocuronium on indication only may be preferred over a continuous deep muscle relaxation, despite the lack of reliable TOF monitoring to ensure adequate depth of relaxation at all times during the procedure. The thoracolaparoscopic esophageal resection consists of two or three phases: an abdominal phase and a thoracic phase and a cervical phase if indicated. Accordingly, depending on the location of the anastomosis, the procedure will start in a prone (thoracic phase) or a supine (abdominal phase) position. Whether the abdominal phase takes places before or after the thoracic phase may influence SRS scores and has never been evaluated. It is uncertain whether a deep NMB has the same advantages during thoracic surgery as during abdominal surgery, because of the rigidity of the ribcage, which keeps the surgical field open. This double-blind randomized controlled study aims primarily to evaluate the use of two muscle relaxant regimes on operating (SRS) and anaesthesiologic conditions in patients undergoing thoracolaparoscopic esophageal resection.

## Methods

The protocol of this study was approved by the local ethics committee (Academic Medical Center, registration number 2014_211#B20141036) and registered at ClinicalTrials.gov under number NCT02320734. The study will be conducted in accordance with the principles of the Declaration of Helsinki in the current version of Fortaleza, Brazil 2013 and in accordance with the Medical Research Involving Human Subjects Act (WMO).

### Design

This study is designed as a single-center randomized controlled double-blinded trial. Patients are randomly assigned to receive either continuous infusion of rocuronium 0.6 mg/kg per hour (group 1) or continuous infusion of NaCl 0.9 % 0.06 ml/kg per hour (group 2). This is started immediately after induction. Treatment allocation will be done in a double-blinded fashion (including both the surgeon and the anaesthesiologist), to standard (on indication) versus deep NMB. Blinding will be done by a computerized randomization code. We will randomly assign according to the principle of balanced assignment: the order in which patients are classified to the different groups will be determined in a computer-randomized order. Block randomization will be done and stratified by type of surgery (start in supine or prone position) to correct for any influence of this parameter on the study endpoints. The reasons for withdrawal will be accurately documented in the case report forms. The medication is prepared and labeled by the pharmacy and supplied by the (blinded) researcher to the blinded anaesthesiologist in charge of the patient. Double blinding will be maintained during the study unless the anaesthesiologist in charge needs to unblind the data in case of a medical emergency.

### Patients

Sixty-six patients will be included. Inclusion and exclusion criteria are presented in Table 1. Patients are included only after informed consent is obtained.

**Table 1 Tab1:** Study in- and exclusion criteria

Inclusion criteria	Exclusion criteria
Age of at least 18 years	Age less than 18 or pregnancy
Elective thoracolaparoscopic esophageal resection (either two- or three-stage approach)	Known allergies for aminosteroid-type muscle relaxants or sugammadex
Written informed consent	Severe kidney dysfunction (glomerular filtration rate of less than 30), patients on dialysis
	Liver function disorders
	Myasthenia gravis or other (neuro)muscular diseases
	Carcinomatosis
	Use of anti-epileptica and lithium or drugs containing Kinine

### Study procedures and measurements

Prior to the start of the study, both surgeons will be trained in rating, by practicing the SRS during two procedures, containing about 32 SRS scores. During surgery, operating conditions will be evaluated every 30 min for both the abdominal and thoracic phases by using a 5-point SRS ranging from 1 (poor surgical conditions, intervention necessary) to 5 (optimal surgical conditions) as well as a continuous numeric rating scale ranging from 1 to 100 (Table 2) [2]. Scoring will be done by the two surgeons performing the procedure ([name]). One SRS and one numeric rating score are registered each 30 min (with a variation of 31–40 min if the surgeon’s attention is needed elsewhere). If both surgeons are operating on the same patient, agreement on the score must be reached.

**Table 2 Tab2:** Surgical rating scale

1	*Extremely poor conditions*: the surgeon is unable to work because of coughing or because of the inability to obtain a visible laparoscopic field because of inadequate muscle relaxation. Additional neuromuscular blocking agents must be given
2	*Poor conditions*: there is a visible laparoscopic field, but the surgeon is severely hampered by inadequate muscle relaxation with continuous muscle contractions, movements, or both with the hazard of tissue damage. Additional neuromuscular blocking agents must be given
3	*Acceptable conditions*: there is a wide visible laparoscopic field, but muscle contractions, movements, or both occur regularly, causing some interference with the surgeon’s work. There is the need for additional neuromuscular blocking agents to prevent deterioration
4	*Good conditions*: there is a wide laparoscopic working field with sporadic muscle contractions, movements, or both. There is no immediate need for additional neuromuscular blocking agents unless there is the fear of deterioration
5	*Optimal conditions*: there is a wide visible laparoscopic working field without any movement or contractions. There is no need for additional neuromuscular blocking agents

Surgical rating scale adapted from Martini et al. [2]

If indicated by either surgeon or anaesthesiologist, all patients, irrespective of their group assignment, can receive boluses of open-label rocuronium 0.30 mg/kg. The reason for the on-demand bolus is registered. Surgical conditions will be scored immediately before and 5 min after a bolus when requested by the surgeon only, so as not to affect blinding of the surgeons. Indications for bolus infusion are high peak inflation pressure (>35 mm Hg), high abdominal (>15 mm Hg) and thorax (>8 mm Hg) insufflation pressure, and movement, breathing, or straining of the patient. Intra-abdominal pressure will be registered every 30 min from the abdominal CO_2_ insufflation device.

For neuromuscular function monitoring, the TOF-watch SX acceleromyograph (MSD BV, Haarlem, The Netherlands) will be used. During the procedure, a TOF count (situated at the flexor hallucis brevis of the leg) will be done every 30 min at the same time as the evaluation of the surgical conditions and directly before and 5 min after an on-demand bolus [10]. Both the anaesthesiologist and the surgeon will be blinded for the results of this measurement.

When the operation is finished, a TOF count and ratio are done at the ulnar nerve (not blinded). Depth of NMB will be scored as follows: (1) very deep NMB (post-tetanic count, no twitches, (2) deep NMB (post-tetanic count, one or two twitches), (3) moderate NMB (TOF, one or two twitches), and (4) shallow or no NMB (TOF four twitches, ratio of more than 0 %). In patients with a very deep or deep NMB, a TOF is repeated 30 min after infusion of sugammadex to check for recurarization. Based on the TOF count at the end of operation, sugammadex is given at a dose of 16 mg/kg in very deep block, 4 mg/kg in deep NMB, 2 mg/kg in moderate NMB, and 2 mg/kg in shallow NMB. If recurarization is found, an additional dose of sugammadex is given on the basis of the TOF count found at that time. In case of a clinical reason to continue mechanical ventilation after surgery, administration of sugammadex is postponed until one post-tetanic twitch is found. The sugammadex dose needed in case of a very deep block (16 mg/kg) was added to the protocol after 10 patients.

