#### Secondary parameters

Rating of SRS during thoracic phase of the operation, number of on-demand boluses infused, and indication of on-demand bolus administration.Rating of anaesthesia conditions, including peak and mean respiratory pressures and incidence peak insufflation pressure of more than 35 mm Hg; depth of NBM at the end of surgery, intraoperative cardiac and respiratory incidents; and time until spontaneous breathing and time until extubation after interruption of sedation.Costs: amount of rocuronium used (milligrams), dose of sugammadex needed (milligrams) to reach a TOF of more than 90 %, time to reversal, number of patients (percentage) with recurarization measured 30 min after reversal and consequently the need for additional sugammadex, and duration of surgery and operating room occupancy (expressed in hours and personnel cost per hour) and ICU stay.Perioperative surgical complications.The ability of surgeons and anaesthesiologists to estimate post-operatively to which group the patient was randomly assigned (at the end of each of the two phases).

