The reasons for anaesthesiologists not to standardize a deep NMB regime may be the expected need for reversal at the end of the procedure. When employing deep NMB, one has the option to use sugammadex, which is costly, or have the patient on mechanical ventilation post-operatively, which may increase the incidence of pneumonia following surgery [1]. Reversal with (high-dose) neostigmine is usually not favored following these procedures in fear of the cholinergic effects on the newly formed anastomosis, although recent evidence for the adverse effects on anastomotic patency is scarce and the existing data are conflicting [6–8].

Sugammadex has been shown to be a safe and fast alternative to reverse the neuromuscular blocking induced by rocuronium, even when it was administered continuously for up to 5 h [11]. However, as yet, no data on the use of sugammadex after 8–9 h of deep (continuous) neuromuscular relaxation and the incidence of recurarization exist. Therefore, we will register time until TOF of more than 90 % and the incidence of recurarization.

Furthermore, lack of adequate neuromuscular monitoring (e.g., TOF)—in the prone position but especially in the supine position, where both hands are tucked in alongside the body—is challenging to the anaesthesiologist. Hand movements are often inhibited, and TOF counts are unreliable. In view of that, anaesthesiologists and surgeons often disagree about the operating conditions and the ability of the surgeons to judge whether the patient is adequately relaxed or not. We therefore let the surgeons (and anaesthesiologist) “estimate” at the end of the operation to which group the patient was randomly assigned.

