### Limitations

This study has some unavoidable limitations instigated by the included surgical population and chosen design. During these procedures, TOF count is not reliable in prone positioning and supine positioning, because of the movement confinement of the body. Although this is part of the normal situation anaesthesiologists face during these procedures, we cannot be absolutely sure whether the patients randomly assigned to receive deep neuromuscular relaxation are insufficiently relaxed or too deeply relaxed. Indeed, for adequate neuromuscular relaxation of the diaphragm, a post-tetanic count of between 0 and 1 is probably necessary and this is very hard to accomplish in normal practice. We will use the standard dosing for continuous use that is advised in the product specifics (Summary of Product Characteristics text) of rocuronium and sugammadex. However, because of the lack of data on continuous administration for more than 5 h, there may be variability in NMB seen, and some patients may have a very deep block at the end of the procedure. We therefore amended the protocol after 10 patients, more clearly describing the management of patients with a very deep block at the end of the operation. In addition, we use the peroneal nerve to measure TOF because we expect less movement inhibition. However, it is possible that, owing to positional problems, we cannot get a reliable TOF for every patient. Consequently, we do not adjust the infused rocuronium dose on the basis of these measurements.

Another limitation is that the surgeons might guess in which group the patient is randomly assigned because of high abdominal pressures, respiratory events, or diaphragm movements. This might influence scoring of SRS. A recent study, however, showed that surgeons were not able to estimate the group assignment to deep versus moderate neuromuscular relaxation. They estimated correctly in a little more than 50 % and this can also be explained by chance. We also let the surgeons estimate group assignment to be able to estimate bias in SRS. In addition, we chose for a neuromuscular regime that is common practice (on demand) and compared that with a regime that is not (deep neuromuscular relaxation). Based on the results of the present study we will weigh benefits against costs.

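### The timing of the group guess is described inconsistently, and the text shown does not place the final guess before the open end-of-surgery TOF

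*Protocol article*

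**What the plan says.** **TOF.** Under Study procedures and measurements, the 30-minute TOF readings are concealed: "Both the anaesthesiologist and the surgeon will be blinded for the results of this measurement". The closing reading is treated differently: "When the operation is finished, a TOF count and ratio are done at the ulnar nerve (not blinded". It then guides reversal in both groups: "Based on the TOF count at the end of operation, sugammadex is given", at doses that the same section lists from 2 to 16 mg/kg according to depth.

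**Group guess.** Secondary parameters lists the ability of surgeons and anaesthesiologists to "estimate post-operatively to which group the patient was randomly assigned (at the end of each of the two phases". The Discussion places the guess "at the end of the operation to which group the patient was randomly assigned". Limitations gives the purpose of the surgeons' guess: "We also let the surgeons estimate group assignment to be able to estimate bias in SRS". It takes comfort from a study in which surgeons were right only slightly more than half the time.

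**Blinding.** The Design section says double blinding holds throughout, with a medical emergency as the only exception.

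**Recovery times.** Secondary parameters defines "time until spontaneous breathing and time until extubation after interruption of sedation". Post-operative care allows the tube to be removed in theatre or later in the PACU or ICU.

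**The concern.** By hiding every intra-operative TOF, the plan treats block depth as information that could reveal the arm. The closing TOF is open, and its result shows again in the reversal dose. Background and Limitations both expect continuous infusion to leave some patients with a deep or very deep block, so this reading is a plausible clue to group.

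The guess is meant to show whether blinding held while surgical conditions were being scored. A guess made with the closing TOF in view answers another question, namely whether end-of-surgery depth differs between arms. A high share of correct guesses could then be read as failed blinding when blinding during surgery was sound.

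A smaller matter concerns the recovery times. Their clock starts when sedation is interrupted, a moment that staff choose after randomisation, possibly with the block depth already known. The Background names slow emergence as a worry about continuous infusion, and the Discussion sets time until extubation against any benefit. Time spent sedated between the end of surgery and that moment is outside the defined outcome.

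**Working it through.** **1. Which guesses can follow the open TOF?**

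- *Guess at the end of each phase (one part of Secondary parameters).* The first guess always precedes the closing TOF. In the three-stage operation a cervical phase follows thoracoscopy and laparoscopy, so the second guess precedes it too. In the two-stage operation the thoracic phase is last, so the second guess falls at about the time of the TOF and the order is open.
- *Guess after surgery or at the end of the operation (the other part of Secondary parameters, and the Discussion).* The guess falls at about the time of the TOF in every patient, and the order is open.

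The number of exposed guesses therefore depends on which wording governs.

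**2. How far could the guess be moved?** The documents give no block-depth rates by arm, so this is an illustration. Assume equal allocation and a rater who names group 1 whenever the block is deep or very deep. Then

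accuracy = 0.5 × [P(deep | group 1) + 1 − P(deep | group 2)].

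Assumed ranges are 0.5 to 0.9 for group 1 and 0.05 to 0.5 for group 2:

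- 0.5 and 0.5: 0.5 × (0.5 + 0.5) = 0.50
- 0.5 and 0.3: 0.5 × (0.5 + 0.7) = 0.60
- 0.7 and 0.3: 0.5 × (0.7 + 0.7) = 0.70
- 0.9 and 0.3: 0.5 × (0.9 + 0.7) = 0.80
- 0.9 and 0.05: 0.5 × (0.9 + 0.95) = 0.925

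**3. How often would that look like broken blinding?** Take one final guess from each of 60 evaluable patients, the plan's target before drop-out. That target reproduces: a difference of 0.6, SD 0.7, two-sided 5% and 90% power give 29.6, so 30 per group, by the exact two-sample t calculation. The present point does not otherwise depend on it.

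The article does not say how guesses will be tested. I assume a comparison with one half. The smallest count whose upper binomial tail is at most 0.025 is 39 of 60 (65%); the tail is 0.014 under pure chance. The probability of reaching 39 or more is:

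| True accuracy | P(at least 39 of 60 correct) |
|---|---|
| 0.50 | 0.014 |
| 0.60 | 0.257 |
| 0.70 | 0.838 |
| 0.80 | 0.998 |

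**4. Recovery times.** No figure in the documents bears on this, so only the structure can be shown:

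time from end of surgery to extubation = (end of surgery to interruption of sedation) + (interruption of sedation to extubation).

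The defined outcome is the second term. The first is not reported as an outcome, and its size and any difference between arms are unknown.

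**The case against.** The strongest reply is that the text gives no order at all. A reader might infer that the TOF is read before the anaesthesiologist guesses and before sedation is stopped. No section says either. Fig. 1, the study timeline, is not available here and may bear on the order, and a journal article may leave form order to the full protocol. This stands against any claim that the guess is contaminated. It does not remove the conflict between Secondary parameters and the Discussion, which is in the text shown.

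Second, a reader might infer that the whole blinding check is lost. A first-phase guess must precede the closing TOF, and under the each-phase wording so must both guesses in three-stage patients. The surgeons' guess, the one used to judge bias in the surgical rating scale (SRS), is exposed only if they learn the TOF result or reversal dose first, which is not stated. Anaesthesiologists do not score the SRS. All of this stands.

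Third, the TOF shows depth and not the allocation code. Group 2 may receive open-label boluses, and group 1 is expected to vary. The reading may therefore be a weaker clue than it first appears, which is why the illustration starts at 0.50.

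Fourth, a reader might infer that the extubation outcome is biased and needs a new time zero. The documents do not support this. No section says that sedation continues while reversal is awaited, and the open TOF is needed to guide reversal in both arms. Starting at interruption of sedation is a defensible way to isolate emergence. Some delay would also show in time to reversal, operating room occupancy and ICU stay. Replacing the clock would bring in ventilation continued for clinical reasons.

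**Conclusion.** The point holds in a limited form. The sections on the group guess disagree about its timing, and the text shown leaves the final guess free to follow an open reading that may hint at the arm. If it does follow, the anaesthesiologist's final guess is not a clean check of intra-operative blinding, and sound blinding could be reported as broken.

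The size is unknown. The accuracy range of 0.50 to 0.925, and the 0.257 to 0.998 chance of a significant result at accuracies of 0.60 to 0.80, rest on assumed depth rates, a rater who simply follows the TOF, and 60 independent guesses.

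The primary outcome is untouched, because the abdominal SRS is scored during surgery, before the closing TOF. For the recovery times, the documents support only a supporting analysis: sedation may be stopped by staff who have seen the block depth, but nothing shows that this distorts the defined outcome.

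**What to change.** 1. Reconcile Secondary parameters and the Discussion: surgeon and anaesthesiologist each record a guess at the end of each phase, always before the unblinded TOF is read or the reversal dose is known to them. State the same order beside the closing TOF in Study procedures and measurements.
2. Qualify the blinding statement in Design: for outcomes measured after the closing TOF, staff know the block depth although the allocation code stays concealed.
3. Keep time to spontaneous breathing and time to extubation from interruption of sedation as defined, and report both from end of surgery as supporting figures.

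The cost of items 1 and 2 is wording and the order of entries on the case report form; clinical management does not change. Item 3 needs the time of end of surgery, which recording the duration of surgery should already supply. Its small downside is that the supporting figures include transfer time and clinically planned ventilation, so they should be read beside the defined outcomes and not in their place.

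### The 30-minute recurarization check is scheduled only after deep or very deep block, so this secondary outcome is likely to be looked for more often in the infusion arm

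*Protocol article*

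**What the plan says.** Under Secondary parameters, the cost item includes the "number of patients (percentage) with recurarization measured" at 30 min "after reversal and consequently the need for additional sugammadex". No depth class is named. The Discussion says that the incidence of recurarization will be registered, again without restriction. Its reason is that no data on sugammadex after 8–9 h of "deep (continuous) neuromuscular relaxation and the incidence of recurarization exist".

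Study procedures and measurements sets four depth classes at the end of surgery. Class 1, very deep, has no post-tetanic twitch. The next two are "deep NMB (post-tetanic count, one or two twitches), (3) moderate NMB (TOF, one or two twitches", and the last is "4) shallow or no NMB (TOF four twitches" with a ratio above 0%. The sugammadex doses are 16, 4, 2 and 2 mg/kg, so every class is reversed. The 30-min reading is tied to the first two classes: "In patients with a very deep or deep NMB, a TOF is repeated". If recurarization is found, "an additional dose of sugammadex is given on the basis of the TOF count found at that time".

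On expected depth, the Background says of continuous rocuronium that "this might result in a deep NMB at the end of surgery". The Limitations add that some patients may end with a very deep block.

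**The concern.** The outcome and the measurement schedule do not cover the same patients. A patient with a moderate or shallow block is reversed and falls within the outcome as listed, yet has no planned reading from which it could be scored.

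This matters because the class that triggers the check is a post-randomisation state that treatment may influence. If more patients in group 1 end deep, more of them are checked. Counting over all patients then treats the unchecked as event-free, and more of those are likely to be in group 2. Counting over checked patients compares subsets that treatment helped to form, and the group 2 subset may be very small. An analysis plan can choose the denominator but cannot recover readings that were never taken.

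A smaller problem sits at the same boundary. A TOF count of 0 with three or more post-tetanic twitches fits no class, so neither its dose nor its check is fixed.

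**Working it through.** The documents give no figure for recurarization or for the depth distribution, so there is no stated result to reproduce. The check has three parts.

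**1. Map every end-of-surgery state to the scale and schedule (Study procedures and measurements).**

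| State | Class | Sugammadex | 30-min check |
|---|---|---|---|
| TOF 0, no post-tetanic twitch | very deep | 16 mg/kg | yes |
| TOF 0, post-tetanic count 1–2 | deep | 4 mg/kg | yes |
| TOF 0, post-tetanic count 3 or more | none | not stated | not stated |
| TOF 1–2 | moderate | 2 mg/kg | none scheduled |
| TOF 3 | none | 2 mg/kg by either neighbour | none by either neighbour |
| TOF 4 | shallow or none | 2 mg/kg | none scheduled |

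Two states have no class. Only the first lies where the choice changes dose and check.

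**2. Effect of unequal checking on the recurarization percentage.** Input from the document: 66 patients, so 33 per arm if balanced. Assumed inputs: share in the two deepest classes 70% in group 1 (range 50–90%) and 20% in group 2 (range 10–30%); risk 10% in those classes.

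Reported percentage over all patients = share checked × risk.

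- Group 1: 0.70 × 10% = 7.0%, or 33 × 0.07 = 2.3 patients.
- Group 2: 0.20 × 10% = 2.0%, or 33 × 0.02 = 0.7 patients.
- Ratio 7.0/2.0 = 3.5. Over the assumed ranges it runs from 0.50/0.30 = 1.7 to 0.90/0.10 = 9.0. If both arms were checked equally often it would be 1.

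True percentage = share checked × 10% + share unchecked × risk in unchecked classes.

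- Same risk (10%): 10% v 10%, ratio 1.0. The reported contrast is wholly artefact.
- Half the risk (5%): 0.70 × 10 + 0.30 × 5 = 8.5% v 0.20 × 10 + 0.80 × 5 = 6.0%, ratio 1.4.
- No risk: 7.0% v 2.0%. The reported figures are right.

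Over checked patients only, group 2 would supply 33 × 0.20 = 6.6, about 7 patients (33 × 0.10 = 3.3 to 33 × 0.30 = 9.9). With no events among m patients, the exact two-sided 95% upper limit is 1 − 0.025^(1/m): 41% for m = 7, 71% for m = 3, 31% for m = 10. Such a subset says little.

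**3. Effect of the unclassified state on dose.** The choice is between 4 and 2 mg/kg. At an assumed 80 kg this is (4 − 2) × 80 = 160 mg per patient (120 mg at 60 kg, 200 mg at 100 kg). The cost analysis leaves out the first 10 patients, so 66 − 10 = 56, or 28 per arm if balanced. One such patient moves an arm mean by 160/28 = 5.7 mg (120/28 = 4.3 to 200/28 = 7.1).

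**The case against.** The strongest reply is that the two sections can be read together: one names an outcome measured at 30 min, the other says in whom it is measured, and the result is number found over number checked. The Discussion supports this, since the evidence gap it names concerns long, deep, continuous block. As a description of recurarization after deep block that reading is sound, and it means the listed outcome need not be reported over all patients. But neither section states that denominator, and the reading leaves a comparison of arms resting on subsets that treatment helped to form.

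Several stronger readings are tempting but not supported:

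- A reader might infer that recurarization cannot be recorded, or re-dosing triggered, after moderate or shallow block. The re-dosing rule is not limited to the deeper classes, so clinically evident cases could still be found and treated, and need for re-intubation is collected in everyone. What is missing is a scheduled check, so subclinical cases are likely to be missed.
- A reader might infer that group 1 will fill the deep classes. The protocol says only that this might happen, and both arms may receive rocuronium boluses of 0.30 mg/kg, which can leave control patients deep and narrow the contrast.
- A reader might infer that the trial will test recurarization between arms over all patients. The Statistical analysis section promises only additional analyses of the secondary outcomes.
- A reader might treat the missing class for TOF count 3 as a comparable fault. It changes neither dose nor check.

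**Conclusion.** The point holds as a mismatch between an outcome listed without restriction and a check scheduled by a post-randomisation state. Detection of subclinical recurarization is likely, though not certain, to be more frequent in group 1, and any between-arm contrast would partly reflect that.

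The size cannot be learned from the documents. Under the assumed shares and risk, the artefact runs from nil, if moderate and shallow blocks carry no risk, to the whole apparent ratio of 3.5 (1.7 to 9.0 over the assumed shares), if all blocks carry the same risk. The expected counts are small, about 2.3 and 0.7 patients, so little could be concluded about a difference between arms in any case. The value of the change lies in an honest incidence figure, which the Discussion gives as a purpose of recording it.

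This is one item within a secondary cost outcome. The primary SRS comparison is unaffected, and the effect on sugammadex cost is small. The unclassified state at the deep–moderate boundary is real but minor, and its frequency is unknown. The change is worth making because it is cheap and the missing readings cannot be recovered later.

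**What to change.** - Repeat the TOF 30 min after sugammadex in every reversed patient in both arms, whatever the depth class.
- For patients already operated on without the check, report recurarization as number found over number checked, by arm and depth class, with no between-arm test.
- As a minor addition, score a TOF count of 0 with three or more post-tetanic twitches as deep, with 4 mg/kg and the 30-min check.

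The cost is one extra reading per moderate or shallow patient with the device already in use: at most 66 readings, and fewer because recruitment has started. It also needs a protocol amendment. The class assignment is a dosing rule and needs clinical agreement. If the extra reading is refused, the minimum is to restrict the outcome in writing to deep and very deep block and state that denominator. That makes the report accurate but does not make the arms comparable.
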